**Figure 1. f1:**
[figure not shown]
Schematic overview of the IMPALA Trial.

The study target is 540 participants (270 participants per intervention group). Participants were recruited across sites from three countries (Uganda, Kenya and South Africa). The list of study sites is available from the trial registration on clinicaltrials.org. The trial population comprises participants with no significant laboratory abnormalities at screening, negative hepatitis B status, willing to adhere to suitable methods of contraception and with no known history of non-nucleoside reverse transcriptase inhibitor (NNRTI) and/or integrase strand transfer inhibitor (INSTI) resistance. The detailed list of inclusion and exclusion criteria is shown in
Table 1.

**Table 1. T1:** IMPALA Trial Inclusion and Exclusion Criteria.

IMPALA Trial Inclusion and Exclusion Criteria	
Inclusion Criteria	
**1.**	18 years of age and above.
**2.**	HIV-1 infection confirmed in clinic records or by study team.
**3.**	Virologically suppressed (HIV VL <200 copies/mL) for ≥3 months prior to randomization visit
**4.**	Is on a first-line oral regimen of 2NRTI + DTG
**5.**	Is identified as a participant with a history of, or at risk of, sub-optimal ART adherence or engagement in care based on one or more of the following criteria: a. Documented detectable HIV-1 viral load (>1000 c/mL) on all-oral ART (EFV/NVP or DTG-based) in the prior 2 years despite being ART-experienced for >3 months. b. History of being lost to follow-up from care (>4 weeks elapsed since a missed scheduled clinic appointment or refill in the prior 2 years). c. Failed to link to HIV care despite ≥3 months elapsed since HIV diagnosis
**6.**	Females: human chorionic gonadotrophin (HCG) negative and willing to use one highly effective form of contraception if WORP
**7.**	Male participants are advised to wear a condom for sexual intercourse.
**8.**	Must sign informed consent form (ICF) indicating that the participant understands the purpose of, and procedures required for, the study and is willing to participate in the study.
**9.**	Willing and able to attend all clinic appointments.
Exclusion Criteria	
**1.**	Not virologically suppressed (VL <200 c/mL) for >3 months at the conclusion of screening process.
**2.**	Previous use, or intention to use, protease inhibitor-based ART at any time.
**3.**	Evidence of prior HIV-1 resistance test with NNRTI drug resistance mutations (other than K103N) and/or INSTI drug resistance mutations.

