### Interventions

Screening for eligible participants is performed, and the baseline visit (Day 1) will occur within 4 months of the first screening visit. After participant information is provided an assessment of understanding is performed. Those who understand the implications of the study and are keen to participate are invited to provide written informed consent and are evaluated for eligibility during the screening period. Participants who are viraemic (HIV-1 VL ≥200 copies/mL) at the time of screening must be virologically suppressed on a regimen of 2 NRTIs + DTG for a minimum of 3 months prior to randomization.

Eligible participants are randomly assigned to one of 2 treatment arms using a computer-generated randomization schedule prepared in advance by the trial statistician. To ensure balance, randomization employs randomly permuted blocks of random block sizes (4, 6, 8, 10, 12) and stratified according to the study site. Based on this randomization code, the study investigational product is packaged and labelled.

On Day 1, virologically suppressed (<200 copies/mL for at least 3 months) individuals are randomized 1:1 to either continue daily oral ART (2 NRTI + DTG, control arm), or switch to Q2M CAB LA + RPV LA IM, the intervention arm. Those randomized to the intervention arm are offered either an optional oral lead in (OLI) of 1 month daily oral CAB and RPV or a direct to injection (DTI) approach. This decision to dose with or without an OLI phase is determined by the study participant following the informed consent discussion with the investigator. Baseline assessments are performed on Day 1.

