### Laboratory procedures

Blood samples are collected for the following tests per the SoA (
Table 2): haematology (complete blood count), CD4+ T cell count, serum chemistry (sodium, potassium, creatinine, liver function tests [LFTs] including alanine transaminase (ALT), aspartate aminotransferase (AST), total bilirubin, alkaline phosphatase (ALP)), a metabolic profile (haemoglobin A1c (HbA1c), fasting cholesterol, fasting triglycerides) and random urine sample for urinalysis. For participants in the CAB LA + RPV LA arm with a positive screening hepatitis B core antibody (HBcAb), repeat LFTs are required at the Month 4 visit. In the control arm, individuals who are switched from NNRTI to DTG during the screening period undergo additional glucose monitoring if required by national guidelines.

The laboratory results are reviewed by the investigator who documents the review and records any clinically relevant changes occurring during the study in the Adverse event (AE) log. Urine pregnancy tests are performed at all study visits for female participants of reproductive potential.

For efficacy assessments, participants in both groups have routine HIV-1 VL monitoring at baseline and Months 6, 12, 18, and 24. Participants in the CAB LA + RPV LA Q2M arm also have HIV-1 VL monitoring at Months 2 and 8, and those in the oral ART control arm have additional HIV-1 VL monitoring at Months 3 and 9.

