### Sample size calculation

Assuming a true 78% virologic response rate in each group, a non-inferiority margin of -10%, and a 2-sided 5% significance level (one-sided 2.5% significance level), this study requires 270 participants per treatment group to provide 80% power to test the hypothesis of noninferiority of CAB LA + RPV LA Q2M vs. daily oral ART. Should non-inferiority be demonstrated, this sample size also provides 80% power to declare superiority of CAB LA + RPV LA Q2M compared with daily oral ART if the difference in virologic response between the treatment arms is 10% (83% CAB LA + RPV LA Q2M vs. 73% daily oral ART).

In addition, this sample size provides at least 80% power for the key secondary non-inferiority hypothesis for virologic failure, with a 2-sided 5% significance level, non-inferiority margin of 4% and assumed virologic failures rates of 4% in CAB LA + RPV LA and 6% in daily oral ART.

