### Objectives and endpoints

The objectives and endpoints of the Study are shown in
Table 3.

**Table 3. T3:** Study Objectives and Endpoints.

Objectives	Endpoints
Primary:	
To demonstrate the non-inferior efficacy of switching to every 2 months (Q2M) intramuscular (IM) injection of cabotegravir (CAB) long-acting (LA) plus rilpivirine (RPV) LA compared with continuation of daily oral ART over 12 months in people living with HIV-1 (PLHIV1) with a history of sub-optimal ART adherence or engagement in care	• Proportion with plasma HIV-1 viral load (VL) <50 c/mL at 12 months (by Food and Drug Administration [FDA] snapshot algorithm)
Secondary:	
To demonstrate the antiviral activity and the impact on retention in HIV care of switching to Q2M CAB LA + RPV LA compared with continuation of daily oral ART over 12 and 24 months in PLHIV1 with a history of sub-optimal ART adherence or engagement in care	• Proportion with confirmed virologic failure (CVF) [plasma HIV-1 VL ≥200 c/mL on 2 consecutive occasions] at 12 and 24 months • Proportion with LTFU [>4 weeks elapsed since their last missed appointment] at 12 and 24 months • Proportion with plasma HIV-1 VL <200 c/mL at 12 months by FDA snapshot algorithm • Proportion with virologic response [plasma HIV-1 VL <50 c/mL] at 24 months by FDA snapshot algorithm • Proportion with virologic non-response [plasma HIV-1 VL ≥50 c/mL] at 12 and 24 months by FDA snapshot algorithm
To demonstrate the immunological activity of switching to Q2M CAB LA + RPV LA compared with continuation of daily oral ART over 12 and 24 months in PLHIV1 with a history of sub-optimal ART adherence or engagement in care	• Change in CD4+ T cell count from baseline (12 and 24 months) • Incidence of HIV disease progression (HIV/AIDS-related hospitalizations, illness, or deaths) (through 24 months)
To evaluate the safety and tolerability of switching to Q2M CAB LA + RPV LA compared to continuation of daily oral ART	• Incidence of adverse events through 12 and 24 months • Incidence of adverse events, Grade 3 and 4 (through 12 and 24 months) excluding injection site reactions (ISRs) • Frequency of ISRs of any grade

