## Statistical Analysis Plan

### Primary Statistical Hypothesis

CAB LA + RPV LA is non-inferior (non-inferiority margin, -10%) in the proportion of participants with plasma HIV-1 RNA <50 c/mL as per FDA snapshot algorithm at Month 12, compared to a daily triple drug oral regimen consisting of 2NRTI + DTG regimen (ART).

Analysis will be undertaken to evaluate primary and secondary objectives of the protocol after all participants have completed their Month 12 visit, and undertaken again once all participants have completed their Month 24 visit. The primary analysis will be conducted using the Month 12 data. No adjustment for multiplicity resulting from repeated evaluation of the primary endpoint will be made, as the Month 24 analyses will be secondary.

For the primary efficacy endpoint analysis, each participant’s virologic response (HIV 1 RNA <50 c/mL) will be calculated according to the FDA’s snapshot algorithm. The primary analysis will be based on the intention to treat (ITT) analysis set. For the primary comparison, the adjusted estimate of the difference in the proportion of participants with virologic response between the 2 groups will be presented along with confidence intervals (CIs), based on an analysis stratified by study site using the Cochran Mantel-Haenszel Method (CMH). Treatment with CAB LA + RPV LA will be considered non-inferior to daily oral ART if the lower limit of the CMH-based 95% CI of the difference in virologic response between the treatment groups is >-10%. Should treatment with CAB LA+ RPV LA demonstrate non-inferiority to daily oral ART, an additional hypothesis testing on the superiority of CAB LA + RPV LA will be conducted. CAB LA+ RPV LA will be considered superior to daily oral ART if the lower limit of the CMH-based 95% CI of the difference in virologic response between the treatment groups is >0%. Since an analysis on the ITT analysis set may not be conservative in a non-inferiority setting, an analysis based on the PP analysis set will also be performed to investigate the impact of excluding participants with major protocol violations and evaluate the robustness of the primary analysis results.

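### Entry allows a viral load of 50-199 c/mL while success requires <50 c/mL, and the primary analysis adjusts for site only, so it gives up precision that the Day 1 viral load could supply

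*Protocol article*

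**What the plan says.** All references are to the Protocol article.

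- **Entry.** Table 1, inclusion criterion 3: "Virologically suppressed (HIV VL <200 copies/mL) for ≥3 months prior to randomization visit". Values of 50-199 c/mL are therefore eligible.
- **Primary endpoint.** Table 3: "Proportion with plasma HIV-1 viral load (VL) <50 c/mL at 12 months (by Food and Drug Administration [FDA] snapshot algorithm").
- **Baseline measurement.** Under Laboratory procedures, "participants in both groups have routine HIV-1 VL monitoring at baseline and Months 6, 12, 18, and 24". Under Interventions, "Baseline assessments are performed on Day 1".
- **Randomisation.** Under Interventions, it is "stratified according to the study site" and by nothing else.
- **Primary analysis.** Under Primary Statistical Hypothesis, the adjusted difference is "based on an analysis stratified by study site using the Cochran Mantel-Haenszel Method (CMH"). The lower 95% limit of this one estimate decides non-inferiority (above -10%) and then superiority (above 0%). The only supporting primary analysis named is on the per-protocol set.
- **Sample size.** "Assuming a true 78% virologic response rate in each group, a non-inferiority margin of -10%, and a 2-sided 5% significance level" leads to 270 participants per group for 80% power.

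**The concern.** The primary hypothesis is about maintaining suppression. Under the entry rule a participant at 120 c/mL is suppressed; under the endpoint rule the same value is a failure. That participant has to improve to count as a success, whereas one entering below 50 c/mL only has to stay there. The Background section describes the related CARES trial as enrolling people suppressed below 50 c/mL. IMPALA widened entry to <200 c/mL and also admits people who were viraemic at screening once they have resuppressed below 200 c/mL, but it defines success at <50 c/mL. The design therefore permits a subgroup that differs from the rest on the variable that defines the outcome.

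A baseline variable of this kind is a natural one to adjust for. Here it is neither a randomisation stratum nor part of the primary estimate, although it is already collected. At stake is the width of the confidence interval that decides the trial, in a design whose power sits almost exactly at 80%.

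**Working it through.** **Inputs from the article:** response 78% in each arm, margin 10 points, one-sided alpha 2.5%, 270 per arm, 7 sites.

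**Assumptions, because the article gives neither figure:** the share *f* entering at 50-199 c/mL, and the response rate *pL* in that group. The rate in the rest is set so that the overall rate stays at 78%: *pH* = (0.78 − *f·pL*)/(1 − *f*).

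**Step 1. Reproduce the plan.**
- Outcome variance = 0.78 × 0.22 = 0.1716.
- n per arm = 2 × 0.1716 × (1.960 + 0.842)² / 0.10² = 269.4, rounded up to 270. The stated figure is reproduced.
- SE at 270 per arm = √(2 × 0.1716/270) = 0.03565, or 3.57 points. The 95% CI half-width is 1.96 × 3.57 = 6.99 points.
- Power = Φ(0.10/0.03565 − 1.96) = 80.1%.

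**Step 2. Add baseline viral load as a stratum.**
- Variance explained = *f*(1 − *f*)(*pH* − *pL*)²; R² is this divided by 0.1716.
- Residual variance *v* = 0.1716 minus the variance explained.
- SE = √(2*v*/270), and power = Φ(0.10/SE − 1.96).

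Worked example, *f* = 10% and *pL* = 55%: *pH* = (0.78 − 0.055)/0.90 = 80.6%. Variance explained = 0.09 × 0.2556² = 0.00588, so R² = 3.4%. Then *v* = 0.16572, SE = 0.03504, half-width 6.87 points, and power = Φ(2.854 − 1.96) = 81.4%.

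| *f* | *pL* | *pH* | R² | Half-width (points) | Power |
|---|---|---|---|---|---|
| site only | – | – | – | 6.99 | 80.1% |
| 5% | 70% | 78.4% | 0.2% | 6.98 | 80.2% |
| 5% | 60% | 78.9% | 1.0% | 6.95 | 80.5% |
| 10% | 55% | 80.6% | 3.4% | 6.87 | 81.4% |
| 15% | 55% | 82.1% | 5.4% | 6.80 | 82.2% |
| 10% | 40% | 82.2% | 9.3% | 6.65 | 83.8% |
| 20% | 50% | 85.0% | 11.4% | 6.58 | 84.6% |
| 20% | 40% | 87.5% | 21.0% | 6.21 | 88.4% |

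Over *f* = 10-20% and *pL* = 40-55%, R² runs from about 3% to 21% and power from about 81% to 88%.

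**Step 3. Check by simulation.** Mantel-Haenszel risk differences with the Sato variance, 7 sites, 540 participants and 4,000 runs per setting, stratified by site versus site × baseline viral load:
- *f* = 15%, *pL* = 50%: power 80.6% vs 83.5%.
- *f* = 15%, *pL* = 60%: power 79.6% vs 80.6%.
- *f* = 30%, *pL* = 50%: power 81.2% vs 87.6%.
- One-sided type I error at the −10% margin, over the three settings: 2.2-2.7% (site only) and 2.2-2.5% (site × viral load).

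Both analyses hold their error rate, and the finer stratification works with 7 × 2 strata.

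**The case against.** The strongest defence is that nothing in the plan is broken. The analysis stratifies by exactly the factor used in randomisation, keeps its type I error, has no systematic bias, and reaches the promised 80% power without baseline viral load. All of this stands. A reader might infer from the gap between the entry and endpoint thresholds that the primary result would be biased or the trial underpowered; the documents and the arithmetic support neither.

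A reader might also count chance imbalance in the 50-199 c/mL share as a further error. Over the same grid it contributes an SD of about 0.7-1.6 points to the unadjusted difference: √(2*f*(1 − *f*)/270) × (*pH* − *pL*). But this is already part of the 3.57-point SE and so already inside the confidence interval. It is the component that adjustment removes, not an addition to it.

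It is tempting, too, to call baseline viral load the strongest available predictor. The documents do not show that. The snapshot endpoint also counts missing data and discontinuation, in people selected partly for past loss to follow-up. The sample size section assumes 22% non-response but only 4-6% virologic failure, and does not split the remainder between low-level viraemia and other causes.

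Finally, the statistical analysis plan is not shown and may contain adjusted or subgroup analyses, so their absence from the article is no finding. That does not remove the point, because the article itself fixes the primary estimator and its single stratification factor.

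**Conclusion.** The point holds as one of efficiency. The primary estimate leaves out a baseline measurement that is already collected and is tied by definition to the endpoint. The site-only analysis remains a valid basis for the trial's conclusion, and the sample size is correct as stated.

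The size of the loss depends wholly on two unknowns. Under the 10-20% and 40-55% assumptions, the cost is about 1 to 8 points of power, or 0.1 to 0.8 points of CI half-width against a 10-point margin. If only 5% enter at 50-199 c/mL and 60-70% of them respond, it is under 0.5 points of power. The textual facts are certain; the magnitude is conditional. The change is worth making because it is cheap and preserves the error rate, not because the present analysis would mislead.

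**What to change.** Before the Month 12 data are analysed, prespecify the primary risk difference in one of two ways:

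- a Mantel-Haenszel difference stratified by site and Day 1 viral load (<50 vs ≥50 c/mL), with a stated rule for sparse strata among the 7 × 2 = 14 cells; or
- a standardised risk difference from a logistic model containing site and the same viral load category.

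Do the same for response <50 c/mL at Month 24 and <200 c/mL at Month 12.

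If the Month 12 comparison between arms has already been seen, keep the site-only CMH analysis as primary and report the adjusted estimate as a labelled sensitivity analysis.

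**Cost:** a short edit to the analysis plan, with no new data and no effect on participants. Enrolment closed on 6 May 2024, so the randomisation strata cannot be changed. The prespecified estimator of an open-label trial would change slightly after enrolment closed, so the amendment should be dated and its timing relative to the interim futility look and any unblinded comparison recorded. Some strata will be small.

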### Safety analyses

The verbatim terms used in the eCRF by investigators to identify AEs will be coded using the Medical Dictionary for Regulatory Activities (MedDRA). Any AE occurring at or after the initial administration of study intervention through the day of last dose plus 30 days is considered treatment emergent. All reported treatment-emergent AEs will be included in the analysis. For each AE, the percentage of participants who experience at least 1 occurrence of the given event will be summarized by the intervention group. Summaries, listings, datasets, or participant narratives may be provided, as appropriate, for participants who die, discontinue intervention due to an AE, or experience severe AEs or SAEs.

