### Intervention arm (CAB LA + RPV LA)

The participants who opt for the OLI Phase receive the study intervention in 2 phases:

*Oral Lead-in (OLI) Phase:* Starting on Day 1, participants receive CAB 30 mg plus RPV 25 mg once daily for 4 weeks to be taken at approximately the same time each day with a meal. The purpose of the OLI Phase is to determine individual tolerability of the combination prior to administration of CAB LA + RPV LA. Both OLI and DTI options have comparable safety and efficacy profiles
^
15
^.

*Maintenance Phase:* After the 4-week OLI Phase, participants return for the Month 1 visit to receive the first IM CAB LA 600 mg + RPV LA 900 mg initiation injections. The second initiation injections with CAB LA 600 mg + RPV LA 900 mg are administered at Month 2, and then continuation injections are administered every 2 months (Q2M) thereafter.

Participants who opt for direct to injection (DTI) (i.e. without the OLI phase) remain on daily oral ART for 4 weeks following randomization. They receive their first initiation injections of CAB LA + RPV LA at the Month 1 visit. The second initiation injections of CAB LA + RPV LA are administered at Month 2, followed by continuation injections CAB LA + RPV LA every 2 months thereafter.

The participants receive CAB LA + RPV LA via two separate 3 ml injections, one administered into each gluteal muscle, using a ventrogluteal approach. The ventrogluteal approach is recommended as the gluteus medius muscle is located away from major nerves and blood vessels
^
16,
17
^, and is more likely to avoid inadvertent subcutaneous administration. Injections are administered by appropriately trained staff and participants must be observed for 10–15 minutes post-injection to monitor for any immediate adverse reactions.

Under exceptional circumstances, to address pre-planned missed CAB LA + RPV LA dosing visits, the use of oral therapy as a “bridging” strategy is permitted. This would usually be in the form of daily oral CAB (30mg) + RPV (25mg), but alternative bridging therapy with local SOC can be considered, for instance when obtaining oral CAB and oral RPV is not practical.

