**Footnotes:**
a. Screening visit 2 is only required if HIV-1 VL ≥200 at screening visit 1 or duration of virologic suppression (HIV-1 VL <200 c/mL) has not reached 3 months. Once a participant is confirmed as virologically suppressed (<200 c/mL), and duration is ≥3 months then randomization should occur within 2 weeks. The screening period must be completed within 4 months. a. One month of oral CAB and RPV (OLI) or continue daily oral ART (DTI) prior to first injections of CAB LA + RPV LA at month 1. b. Perform Month 24 assessments in all participants who withdraw from study intervention prematurely (if participant is willing), and scheduled assessments off the study intervention should be continued up to the Month 24 visit as specified in Section 7.1, Discontinuation of Study Intervention. c. For participants with BMI ≥30 a longer needle should be used as per product administration instructions. d. Adherence assessment and tablet count only in participants receiving daily oral ART, or oral lead-in/bridging treatment in CAB LA + RPV LA group. e. Clinical AEs will be captured from the time of screening. Laboratory abnormalities will not be recorded/reported as AEs till after the baseline visit. f. Detailed healthcare resource data survey to be performed at Month 12 visit, at selected sites only g. From a purposively selected sample at selected sites. h. HIV-1 VL can be repeated on one additional occasion after screening visit 1 if it is still ≥200 c/mL. i. Additional HIV-1 VL testing is performed after 4 (3–6) weeks in participants with VL ≥200 c/mL in CAB LA + RPV LA group; additional plasma sample stored (for batched, blinded viral load testing) after 4 (3–6) weeks in participants with VL ≥200 c/mL in the cART arm; and additional viral load after 12 (10–14) weeks in participants with viral load ≥1000 c/mL in the cART arm; reflex resistance testing is performed on stored plasma sample in participants with VL ≥200 c/mL in the CAB LA + RPV LA group, or ≥1000 c/mL in the cART group. (See also Section 8.1.1.2 for an alternative threshold for testing and definition of virologic failure in the cART group) Pregnant participants in the CAB LA + RPV LA arm who continue the study should have viral load monitoring frequency increased to every 2 months aligned with CAB LA + RPV LA Q2M injection visits during pregnancy and for 6 months following delivery or more frequently as per treating physician preference. Repeat HIV-1 VL testing should be performed after 2–3 weeks in pregnant participants with VL ≥50 c/mL. j. CAB LA + RPV LA arm only k. cART arm only l. Complete blood count: hemoglobin, total white cell count and differential, neutrophil count, platelets. Biochemistry: creatinine, sodium, potassium, alanine transaminase, alkaline phosphatase, total bilirubin, aspartate aminotransferase (at screening only). For individuals switched from NNRTI to dolutegravir during the screening period national guidelines should be followed regarding glycemic monitoring before and after switch. m. Only required for females of reproductive potential n. PBMC stored for baseline archived genotypic drug resistance testing. o. One large size (8–10 mL) EDTA sample stored at the following time-points: at screening, baseline visit, all visits where HIV VL is performed, and each visit where the blood is taken for confirmation of viral load rebound (for additional resistance testing, pharmacokinetic analysis, immune or biomarker tests; both arms); at 1, 3, 6, and 12 months following cessation of CAB LA + RPV LA in participants who develop TB (for drug levels; CAB LA + RPV LA group only); at 1

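### The treatment-emergent AE window (last dose + 30 days) fits neither the 2-month injection interval nor the AE endpoint through Months 12 and 24, and its start for direct-to-injection participants is ambiguous

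*Protocol article*

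**What the plan says.** Safety analyses defines the window once, for both arms: "Any AE occurring at or after the initial administration of study intervention through the day of last dose plus 30 days is considered treatment emergent". It continues: "All reported treatment-emergent AEs will be included in the analysis". The summary is a crude proportion: "the percentage of participants who experience at least 1 occurrence of the given event will be summarized by the intervention group". No exposure adjustment and no other between-arm AE comparison is described. For deaths, discontinuations due to an AE, severe AEs and SAEs, further summaries, listings or narratives are optional.

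The dosing that the window must fit is in the Interventions sections:

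- **Oral lead-in:** "Starting on Day 1, participants receive CAB 30 mg plus RPV 25 mg once daily for 4 weeks".
- **Direct to injection:** participants "remain on daily oral ART for 4 weeks following randomization". Then: "They receive their first initiation injections of CAB LA + RPV LA at the Month 1 visit".
- **Who chooses:** "This decision to dose with or without an OLI phase is determined by the study participant".
- **After the two initiation injections:** one injection visit every 2 months; the Table 2 injection row runs to Month 24.
- **Comparator arm:** daily oral ART to Month 24.

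Table 3 sets the safety endpoint as AE incidence through 12 and 24 months, without restricting it to a treatment window. The Table 2 footnotes keep participants who stop the intervention under scheduled assessment to Month 24. They also plan plasma samples for drug levels "at 1, 3, 6, and 12 months following cessation of CAB LA + RPV LA in participants who develop TB".

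**The concern.** A 30-day tail after the last dose suits a daily pill, because it extends 30 days beyond a dosing interval of one day. Applied to an injection given every 2 months, it closes about halfway through the interval that the injection is meant to cover. A participant who declines the next injection at its scheduled visit has then already been outside the window for about a month. The AEs most informative about tolerability, those that end treatment, can therefore fall outside the count in the long-acting arm while their oral-arm counterparts fall inside it.

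The start raises a second question. The article does not define study intervention. Control participants continue their existing regimen, and direct-to-injection participants do the same for 4 weeks, so the date of initial administration is unclear for both.

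Safety and tolerability compared with daily oral ART is the secondary hypothesis. The AEs at issue are collected in any case, so the counting rule alone decides whether they reach the comparison.

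**Working it through.** The plan gives no figure on this point to reproduce, and no sample size or power depends on it. The check is calendar arithmetic plus one simple model.

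**Inputs from the article:** the window (Safety analyses); the 2-month interval and the 4 weeks on oral ART (Intervention arm); the ±7-day visit window and visit schedule (Table 2, as read from the PDF).

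**Assumptions, because the article gives no values:** early stopping 5% to 20%; direct-to-injection share 25% to 100%; true risk of at least one AE by the cut 30% or 60%.

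**1. End of window**
- Two months = 2 × 365.25/12 = 60.9 days.
- Uncovered: 60.9 − 30 = 30.9 days; 30.9/60.9 = 51%.
- If both visits use the ±7 days: 60.9 − 14 − 30 = 16.9 days to 60.9 + 14 − 30 = 44.9 days.
- An AE on day 45 after the last injection is outside the window even if it is the reason for stopping. In the oral arm, an AE on the day of stopping is always inside.

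**2. Who is affected**
- The window is continuous from first to last dose, so gaps between injections are covered.
- The interval between the two initiation injections is one month, so the 30-day tail essentially covers it.
- Table 2 shows an injection at Month 24, so completers lose nothing.
- That leaves early stoppers, who lose about one month each. Average loss over the arm = stopping share × 1/12:
  - Month 12: 0.05/12 = 0.4% to 0.20/12 = 1.7%.
  - Month 24: 0.05/24 = 0.2% to 0.20/24 = 0.8%.

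**3. Start of window for direct-to-injection participants**
- If only CAB/RPV is study intervention: 28/365.25 = 7.7% of 12 months and 28/730.5 = 3.8% of 24 months are lost.
- If continued oral ART is study intervention: the loss is zero.
- Oral lead-in participants start CAB + RPV on Day 1 and lose nothing on either reading.

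**4. Effect of the first reading in step 3 on the reported percentage**

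With a constant hazard and one full month lost, a participant with true Month 12 risk P is counted with probability 1 − (1 − P)^(11/12).
- P = 30%: 1 − 0.70^(11/12) = 27.9%, a fall of 2.1 points if all are direct to injection, and 0.25 × 2.1 = 0.5 points if a quarter are.
- P = 60%: 1 − 0.40^(11/12) = 56.8%, a fall of 3.2 points, or 0.8 points at a quarter.
- At Month 24 the exponent is 23/24 and the falls are about half of these.

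**5. Endpoint against rule**

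Table 3 counts AEs to a calendar cut. Safety analyses counts AEs to last dose + 30 days. For anyone who stops early, in either arm, the two give different counts, although assessments continue to Month 24.

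**6. Ascertainment**

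AEs are asked about at every visit. Counting baseline, Table 2 schedules 14 visits in the long-acting arm and 9 in the oral arm; after baseline and up to Month 12, it is 7 against 4.

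**The case against.** The strongest reply is that the effect is small, confined to early stoppers, and without clear direction. Most of this stands.

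- **Early stoppers only.** The 51% is a share of one interval in a subgroup of unknown size; over the whole arm it shrinks to the figures in step 2.
- **The oral arm is truncated too.** Oral participants who stop also lose later AEs to the 30-day rule. The difference lies in how the cutoff relates to the dosing interval.
- **The start may cost nothing.** Oral ART has to count as study intervention for the control arm to have any window. If it also counts for direct-to-injection participants, there is no loss. Even on the other reading, the omitted AEs occur on unchanged oral ART before any CAB/RPV, so the fault would be unequal time at risk, not missed harm from the injections.
- **Some events may surface elsewhere.** AE discontinuations and SAEs may be listed or narrated, but this is optional and is not a between-arm comparison.
- **The drug-level sampling to 12 months is limited** to participants who develop TB. It shows that exposure beyond 30 days is anticipated, but it is no general follow-up rule.

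A reader might infer that AEs in the long-acting arm are under-counted relative to oral ART, and that the rule therefore favours CAB LA + RPV LA. The article does not support that: the more frequent long-acting visits push the other way, and neither effect can be sized from the text. Nor does it support a definite late start for direct-to-injection participants, since that turns on an undefined term. The full protocol and SAP, not shown, may define arm-specific dates.

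What remains is that the article states one explicit cutoff for two very different dosing intervals, and that this cutoff does not match its own endpoint. More frequent visits do not cure that.

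**Conclusion.** The point holds as a mismatch and an ambiguity. The stated window omits about 31 of 61 days (51%) of the final injection interval for long-acting participants who stop early, including AEs that lead to declining the next injection. It also departs from the Table 3 endpoint in both arms. Averaged over the long-acting arm, the end of the window costs about 0.4% to 1.7% of 12 months, assuming 5% to 20% stop early. The start costs each direct-to-injection participant either 4 weeks or nothing, depending on what counts as study intervention. On the first reading, the Month 12 percentage with an AE falls by 0.5 to 3.2 points under the assumed risks and shares.

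A net bias towards the long-acting arm is possible but not shown. No primary or key secondary conclusion depends on this rule. It should be fixed because it selectively drops collected events from a comparison that the secondary hypothesis rests on.

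**What to change.** - **Between-arm comparison:** count every AE with onset from Day 1 (randomisation) through the Month 12 and Month 24 cuts, by randomised arm. This matches Table 3 and removes the dependence on the undefined term.
- **On-treatment summary, if kept:** start it on Day 1 in both arms, and extend its end in the long-acting arm to cover at least the full dosing interval after the last injection.

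The cost is analysis wording and programming. AEs are already recorded at every visit, and off-intervention assessments already run to Month 24. The downsides are a slightly higher reported AE rate in the long-acting arm and some off-treatment events in the randomised-arm summary, which the on-treatment summary would help readers to separate.
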